## Abstract

**Background:**

Inappropriate eating behaviors, particularly a lack of food diversity and poor diet quality, have a significant impact on the prognosis of certain chronic conditions and exacerbate these conditions in the community-dwelling elderly population. Current dietary interventions for the elderly have not adequately considered the nutritional needs associated with multiple chronic conditions and personal dietary preferences of elderly individuals. A personalized recommendation system has been recognized as a promising approach to address this gap. However, its effectiveness as a component of an elderly-targeted dietary intervention in real-world settings remains unknown. Additionally, it is unclear whether this intervention approach will be user-friendly for the elderly. Therefore, this study aims to examine the effectiveness of a personalized meal recommendation system designed to improve dietary behavior in community-dwelling elders. The implementation process in terms of System usability and satisfaction will also be assessed.

**Methods:**

The trial has been designed as a 6-month, non-blinded, parallel two-arm trial. One hundred fifty community-dwelling elders who meet the eligibility criteria will be enrolled. Subjects will be allocated to either the intervention group, receiving personalized meal recommendations and access to corresponding food provided as one component of the intervention, as well as health education on elder nutrition topics, or the control group, which will receive nutritional health education lectures. Outcomes will be measured at three time points: baseline at 0 months, 3 months, and 6 months. The primary outcomes will include dietary diversity (DDS) and diet quality (CDGI-E) of enrolled community-dwelling elders, representing their dietary behavior improvement, along with dietary behavior adherence to recommended meals. Secondary outcomes will measure the perceived acceptability and usability of the personalized meal recommendation system for the intervention group. Exploratory outcomes will include changes in the nutritional status and anthropometric measurements of the community-dwelling elders.

**Discussion:**

This study aims to examine the effectiveness, acceptability, and usability of a personalized meal recommendation system as a data-driven dietary intervention to benefit community-dwelling elders. The successful implementation will inform the future development and integration of digital health strategies in daily nutrition support for the elderly.

**Trial registration:**

Chinese Clinical Trial Registry ChiCTR2300074912. Registered on August 20, 2023, https://www.chictr.org.cn/showproj.html?proj=127583

**Supplementary Information:**

The online version contains supplementary material available at 10.1186/s13063-023-07865-1.

## Introduction

### Background and rationale {6a}

China is stepping into a super-aging society with an elderly population over 60 years old expected to take the proportion of 28% by the year 2040 [1]. Keeping a healthy dietary behavior is a crucial step to promote healthy aging, as it plays a significant role in regulating metabolism, reducing age-related comorbidities and functional impairments, and facilitating adequate nutritional intake [2, 3]. However, with a higher chance of multiple chronic conditions (MCCs), functional disability, and limited activities of daily living (ADLs) capacity, the elderly are less likely to keep healthy eating behaviors. Specifically, faced with difficulties in food preparation, limited access to fresh and nutritious foods, and reduced appetite and chewing function, it is difficult for the elderly to consume a wide range of food groups to achieve high dietary diversity [3–5]. The diet quality of the elderly population is also a concern, which not only refers to the adequate achievements of essential nutrients and food variety but also incorporates avoiding unhealthy food choices to be a good alignment in dietary guideline recommendations [6, 7]. Low dietary diversity and diet quality can detrimentally affect the prognosis of certain MCCs and exacerbate the health conditions of the elderly population [5, 7, 8], thus leading to a self-perpetuating cycle of deteriorating health conditions and unhealthy diet. So far, inappropriate eating behaviors have put over 10% Chinese elderly population at risk of malnutrition [9].

Currently, 80% of the Chinese elder population (> 65 years) are now community-dwellers (i.e., living outside nursing homes or hospitals) [10], and dietary interventions targeting the elderly population are encouraged to be placed in community settings to enhance public health impact and resource accessibility. Existing community-based or home-based nutrition support services provide uniformed meal services or nutrition education to help the elderly population get access to nutritious food or increase produce intake [11, 12] yet are unable to meet the personal needs of elderly individuals, resulting in inadequate penetration and effectiveness [2, 12]. The eating behaviors of older adults are influenced by various factors, such as social and cultural contexts, pathophysiological conditions, and physiological changes. This indicates that dietary interventions targeting the elderly population should take a comprehensive consideration of specific nutritional requirements associated with MCCs, personal dietary preferences, medication usage, and their degrading functions of chewing and tasting. In addition, more than 50% of Chinese community-dwelling elders have limited nutrition literacy [13, 14], which hinders them to make informed food choices and achieve a well-rounded diet merely supported by meal services [15, 16].

A personalized food recommendation system aims to utilize comprehensive personal information and food knowledge to provide customized food recommendations [17, 18]. This system has been successful in improving the eating habits of hospitalized elderly patients and offering online restaurant recommendations to the general population [19, 20]. However, current food recommendation systems have yet well address the complex needs of elderly individuals in terms of nutrition, preferences, and ease of use [3, 21, 22]. These elements, however, are the key to community-based daily nutrition support targeted at the elderly population [2, 3]. To address this gap, we developed a personalized meal recommendation system to assist community-dwelling elders in dietary behavior improvement. This system is driven by the knowledge learned from the survey data of community-dwelling elders’ health status and history of diseases and personal dietary preferences, added with information regarding food composition and elderly nutrition guidelines [23]. The simulation experiments results provide evidence that this system is promising in improving the diet quality and food diversity of community-dwelling elders compared to their history of eating behaviors [23]. However, no practical interventions have been developed based on this system to incorporate all essential considerations mentioned above to improve the eating behaviors of community-dwelling elders. Therefore, it is still unclear about the clinical or public health impact of this innovative dietary intervention on the elders’ dietary behaviors in real-world community settings. The acceptability and user experience of implementing this intervention also remains to be articulated.

### Objectives {7}

To address the existing challenges in managing dietary behaviors among the Chinese community-dwelling elders, we have developed a personalized dietary behavior intervention pipeline featuring the automated generation of meal recommendations. The objectives of this trial are (1) to evaluate the effectiveness of personalized meal recommendations on primary outcomes of dietary behavior changes in community-dwelling elders during a 6-month intervention period, while also examining its impact on the nutritional status and anthropometric measurements of the elderly as additional outcomes, and (2) to assess the implementation process of our personalized meal recommendation system as a dietary intervention, including its perceived acceptability and usability as secondary outcomes.

### Trial design {8}

This experimental study expected to run from July 2023 to September 2024 will follow a non-blinded, paralleled, two-arm pre-test post-test design including 150 community-dwelling elders. This trial will be conducted simultaneously in six community health service centers within Nanhu district, Jiaxing City, located in Zhejiang province, China. Following a cluster randomization design, intervention and control sites will be allocated in a 1:1 ratio based on a randomized allocation sequence generated by a single investigator using R 4.2.0 The intervention period is expected to last for 6 months, following a preparation and recruitment phase. Effect measurements will be conducted at three time points: at the beginning, after 3 months, and after 6 months of the intervention. Implementation measurements will be carried out throughout the study. The trial design follows the SPIRIT checklist (Additional file 1).

## Methods: participants, interventions, and outcomes

### Study setting {9}

The study settings will be established in six community health service centers, strategically located in distinct geographical areas within the Nanhu district. These centers were chosen for their accessibility and convenience for device deployment. The participants are expected to be residents of these respective communities. In this trial, the healthcare professional team consisted of informatics scientists from the Institute of Medical Information, nutrition scientists from Chinese Center for Disease Control and Prevention, and clinicians from Peking Union Medical College Hospital. Participant recruitment and outcome measurements will be performed in the community centers, where community health service centers and elderly-serving canteens are located.

### Eligibility criteria {10}

Individuals are eligible if they meet the following inclusion criteria: (1) aged over 65, (2) being able to communicate independently, (3) able to make independent food choices; (4) able to access community sites to receive interventions; (5) able to take meals independently. Participants would be excluded if they are (1) diagnosed with cognitive impairment, indicated by a Mini Mental State Examination (MMSE) score less than 24, or (2) having dietary restrictions strictly mandated by medical prescriptions due to advanced severity of chronic conditions. This includes but is not limited to conditions like end-stage renal disease requiring strict electrolyte management or conditions necessitating highly restrictive diets. Individuals with common chronic conditions such as diabetes, hypertension, and hyperlipidemia are eligible, as they are expected to benefit from the personalized meal recommendations. Our proposed interventions are tailored to support the dietary management of these conditions, aligning with standard dietary guidelines without imposing severe conflicts.

### Who will take informed consent? {26a}

Eligible elderly individuals will be invited to attend the enrollment session, where trained social workers will explain the study in detail. Considering the potential literacy and functional limitations in this demographic, these social workers will use simplified language and visual aids to facilitate comprehension. Participants will receive a consent package containing clear information about the study’s purpose, procedures, risks, and benefits, as well as the assurance of the confidentiality of their data, which will be accessible only to investigators. They will have ample time for review and understanding. Social workers will answer questions and address concerns, ensuring full understanding before participants sign the informed consent forms. This process will occur before any allocation or baseline assessment.

### Additional consent provisions for collection and use of participant data and biological specimens {26b}

The informed consent has included participants’ permission for the use of collected data. Further analysis of biological specimens does not apply to this study.

## Interventions

### Explanation for the choice of comparators {6b}

Comparators were dietary interventions in the form of elderly-targeted nutritional health education in the format of a series of lectures. This is because the effectiveness of nutritional health education has been proved in relevant studies focusing on elderly nutritional support [21]. In addition, the development of our meal recommendations in integrated intervention also refers to the nutrition guidelines that the lecture materials are derived from.

### Intervention description {11a}

#### Usual nutrition support for the control group

Participants in the control group will receive intervention in the format of nutrition and health education based on Chinese geriatric nutrition guidelines and consensus [13]. The learning objective of health education is to provide community-dwelling elders with essential knowledge about nutrition and geriatric health management. Simultaneously, it aims to stimulate their internal motivation to adopt and maintain healthy eating habits in the long term. Table 1 presents the main content of the health education, including (1) food and nutrients, (2) senior nutrition guidelines, and (3) nutritional status and geriatric diseases. The health education course consists of twelve 30-min lectures covering three topics. Every 2 weeks, healthcare professionals with a nutrition background deliver these lectures. Concurrently, social workers distribute brochures and booklets that condense the lecture notes into easily understandable tips and illustrations. Additionally, all lectures and printed materials are recorded and exhibited in the canteen, fostering the establishment of a healthy food environment.

**Table 1 Tab1:** Elderly-targeted health education content

**Health education topics**	**Themes of courses**
Food and nutrients	Food categories and food diversity
	Energy and macronutrient needs for the elderly
	The role of micronutrients in healthy aging
	Good resources for protein
Chinese geriatric nutrition guideline	Malnutrition risk self-screening
	Dietary patterns for the elderly
	Food processing for seniors
	Dietary supplements
Nutritional status and geriatric-associated conditions	Hypertension
	Diabetes
	Osteoporosis
	Sarcopenia

#### Integrated nutrition support with personalized recommendations for the intervention group

Participants in the intervention group will receive integrated interventions that comprise three components: (1) health education with an emphasis on elderly nutrition, (2) personalized dietary advisory service powered by a knowledge-based meal recommendation system, and (3) a healthy food-providing service. Three roles are involved in this process: health professionals, community social workers, and community-dwelling elders. The community-dwelling elders serve as participants to improve their dietary behaviors. Meanwhile, the health professionals and social workers assist by facilitating the promotion of dietary changes through implementing health education and providing instructions on using the meal recommendation system.

#### Theoretical underpinnings

A logic model is a visual roadmap that depicts an intervention study’s components, activities, and intended outcomes in the short term, medium term, and long term, meanwhile revealing the cause-and-effect linkage. Figure 1 shows the logic model of this study. The intervention components and outcome measures are included in the “activities” box. The expected short-term outcomes (knowledge, motivation, perceived behavioral control), medium-term outcomes (dietary behavior improvement, adherence to recommendations), and long-term outcomes (nutritional status, physical functioning, and chronic condition prognosis) were informed by the logic model.

**Fig. 1 Fig1:**
[figure not shown]
Logic model of dietary interventions targeting community-dwelling elders

#### Development and deployment of a meal recommendation system

The objective of a personalized meal recommendation system is to empower community-dwelling elders in their meal-planning endeavors by offering personalized food selection suggestions based on their dietary preferences and health conditions (Fig. 2). To incorporate the specific nutritional needs related to various medical conditions and individual dietary preferences, we have developed user-profiles and a food knowledge base to support the recommendation system.

**Fig. 2 Fig2:**
[figure not shown]
Personalized meal recommendation pipeline

User profiles are built to extract individualized dietary preferences and restrictions. Enrolled community-dwelling elders completed a baseline survey to collect their sociodemographic information, disease and health condition information, and dietary preferences. Additionally, the dietary behaviors of the community-dwelling elders will be tracked for 1 month under natural conditions before the formal recommendation procedure. This tracking period allows for the generation of their preferred dishes, which can be further transferred as another component of their personal dietary preferences. A food knowledge base has been developed and stored as a food knowledge graph, which encompasses information on five core concepts: dishes, ingredients, categories of ingredients, nutrients, and diseases, along with their corresponding attributes and intercorrelations. The knowledge base comprises a total of 180 dishes made from 120 ingredients, encompassing 27 essential nutrients. Furthermore, 30 common geriatric diseases were included to establish disease-related nutrient rules to build the system’s recommendation capabilities. The recommendation algorithm can be divided into three steps: filtering inappropriate dishes, refining preferred dishes, and generating candidate combo meals (a combination of several dishes) generation. First, diseases and health condition information are acquired from user profiles, so that disease-related constraining rules can be used to filter out the candidate dishes containing inappropriate ingredients for the elder individuals. Second, personal dietary preferences, present as top frequently selected dishes, are extracted from tracked eating behavior history to further help pop up most similar candidate dishes in terms of ingredients. Finally, several candidate dishes from different categories are combined as a meal (combo meal). Among all candidate combo meals, the top 5 combo meals will be selected as recommendation outputs according to the nutrient adequacy following the elderly nutrition guideline. The entire recommendation system will be deployed in the checkout system at a community canteen that serves community-dwelling elders on weekdays. During the intervention period, each elder will be given a card to swipe for identification at the beginning of the food selection process. At the same time as identification, they will receive a reminder informing them of five sets of recommended combo meals. Despite the provided dietary suggestions, participants will still be able to choose their preferred dishes voluntarily.

### Criteria for discontinuing or modifying allocated interventions {11b}

The assigned interventions in either group will be discontinued upon the subjects’ request to withdraw from the trial. No modification of the intervention is anticipated throughout the trial.

### Strategies to improve adherence to interventions {11c}

In this trial, adherence primarily refers to the participants’ acceptance and compliance with the recommendations. The degree of their adherence can be objectively measured by the concordance between the actual food choices of elderly individuals and the recommendations provided by the system. Several actions can be taken to enhance compliance, including (1) designing an elderly-friendly interaction process for food recommendations, (2) organizing successive health education courses to boost motivation and raise awareness among community-dwelling elders regarding the importance of maintaining a healthy diet, (3) providing regular updates on personal dietary behavior as feedback and as a trigger for further improvement, and (4) conducting follow-ups by healthcare professionals to enhance adherence to the interventions.

### Relevant concomitant care permitted or prohibited during the trial {11d}

No concomitant care or interventions are not allowed during the trial.

### Provisions for post-trial care {30}

Post-trial care is not applicable for this trial.

### Outcomes {12}

The primary outcome is the dietary behavior changes, specifically defined as dietary diversity, diet quality, and adherence to dietary interventions, from baseline (T0) to 3 months (T1) and 6 months (T2). The key secondary outcome is the perceived acceptability and usability of personalized meal recommendations as a dietary intervention specifically in the intervention group. The exploratory outcomes are nutritional status and anthropometric measurements of the community-dwelling elders.

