### Sample size {14}

This study uses a randomized, non-blinded, two-armed study design with three times measurements during the study. The power calculation is based on the primary outcome measure- dietary diversity score. The sample size was calculated according to the repeated-measures formula [24, 25]: *N* = $$\frac{2{({{\text{Z}}}_{1-\mathrm{\alpha }/2}+ {{\text{Z}}}_{1-\upbeta })}^{2} {\upsigma }^{2}}{k{\updelta }^{2}}$$. In this formula, parameters denoting the number of repeated times *k* = 3, type I error rate *α* = 5% (two-sided), and a power level of 0.80. We set the smallest detected meaningful difference *δ* = 2.3 according to experts’ experience. Based on the results of relevant studies and our baseline survey, the correlation coefficient among measures *ρ* = 0.7, and equal standard deviation *σ* = 6.12 was used [24, 26]. It was estimated that the desired number of included participants at baseline should be set at a minimum of 60 for each arm. Consequently, a total of 150 community-dwelling elderly individuals are expected to recruit at baseline considering an attrition rate of 20% [27–29].

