## Data collection and management

### Plans for assessment and collection of outcomes {18a}

All primary and secondary outcomes will be repeatedly measured at baseline, 3 months, and 6 months. System usability and satisfaction will only be evaluated in the intervention group, while dietary behaviors (dietary diversity and diet quality, adherence to the interventions), nutritional status, and anthropometric measurements will be evaluated in both the intervention and control groups. Detailed information on data collection methods is shown in Table 2.

**Table 2 Tab2:** The outcome measures and collecting methods

**Outcome measure**		**Collection method**
Dietary behavior	Dietary diversity	IoT system log, DDS
	Diet quality	IoT system log, CDGI-E
	Recommendation adherence	IoT system log
System usability and satisfaction	Satisfaction ratings	Questionnaire (CSAT)
	Ease of use ratings	Questionnaire (CES)
Nutritional status	Risk of malnutrition	Questionnaire (MNA-SF)
Anthropometric measurements	Body mass index	Basic body measurement (body weight scale, height rod)
	Waist circumference	Basic body measurement (measuring tape)
	Systolic blood pressure	Blood pressure monitor
	Diastolic blood pressure	Blood pressure monitor
	Skin folds	Basic body measurement (skinfold caliper)

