### Dietary behavior

The assessment of dietary behavior encompasses three main aspects: dietary diversity, diet quality, and adherence to recommended meals. These three components are calculated based on the actual eating behaviors of elderly individuals. To track the food selections of community-dwelling elders, an IoT-based system is deployed in this trial. This system allows for the simultaneous tracking of the dishes chosen by elderly individuals for each meal, along with the check-out process. Dietary diversity will be evaluated using the dietary diversity score (DDS) [30], which has been successfully utilized to assess dietary diversity among the Chinese elderly population [31]. The diet quality of enrolled community-dwelling elders will be evaluated using China Elderly Dietary Guidelines Index (CDGI-E) [32], which is developed based on the elderly-related diet recommendations of the 2016 Chinese Dietary Guideline [33]. CDGI-E has been employed as a dietary quality evaluation index in a large-scale cross-sectional survey conducted nationwide to assess the dietary quality of the elderly [32]. Recording the actual eating behaviors allows investigators to determine the number and quantity of specific food categories in selected dishes. This information facilitates the calculation of the DDS and CDGI-E scores. Adherence to recommended meals is assessed by comparing the dishes selected by elderly individuals with the recommended ones, and the degree of adherence is recorded as the average number of matching choices to the total choices pre week.

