## Statistical methods

### Statistical methods for primary and secondary outcomes {20a}

Statistical analysis will be conducted using R (version 4.2.0; R Foundation for Statistical Computing). We will use a two-sided significance level of 5% and report the results with two-sided 95% confidence intervals (CIs) for all statistical analyses. For continuous variables, the Shapiro-Wilk test and Levene’s test will be utilized to identify the appropriate data treatment (i.e., parametric or non-parametric analysis), followed by a descriptive analysis presenting as means (SD) or median (IQR). Categorical variables will be presented as frequencies (percentages). For the statistical analysis of repeated outcome measures, generalized linear mixed models (GLMMs) will be used. These models are well-suited for our study design as they can effectively handle the complexities of repeated measures data and accommodate various response variable distributions, including normal, nonnormal, and ordinal categorical responses [37–39]. The primary fixed effects in our models will be the intervention and the time. To account for individual variability among participants, random effects will be included in the model to capture the individual variation. We will adjust for potential confounders that might influence the relationship between the intervention and the outcomes. These confounders include both basic demographics (age, gender, and education level) and heatlh-related factors (physical activity level, diet, smoking status, and medication use). We will further consider the inclusion of interaction terms in our model to examine if the effect of the intervention varies across different levels of confounders.

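### Adherence is a primary outcome with no baseline or control-arm value as the protocol defines it, and the two remaining primaries (DDS and CDGI-E) are unranked with no primary time point

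*Protocol article*

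**What the plan says.** All references are to the protocol article.

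- **Outcomes {12}:** "The primary outcome is the dietary behavior changes, specifically defined as dietary diversity, diet quality, and adherence to dietary interventions". Each is a change from T0 to T1 (3 months) and T2 (6 months). Neither follow-up time is marked as the deciding one.
- **Abstract, Methods:** "The primary outcomes will include dietary diversity (DDS) and diet quality (CDGI-E) of enrolled community-dwelling elders", with adherence to recommended meals added. The abstract uses the plural and gives no order.
- **Plans for assessment {18a}:** all primary outcomes are measured at baseline, 3 and 6 months. The dietary behaviors ("dietary diversity and diet quality, adherence to the interventions") are to be evaluated in both groups.
- **Dietary behavior (under {18a}):** "Adherence to recommended meals is assessed by comparing the dishes selected by elderly individuals with the recommended ones". Section {11c} gives adherence the same meaning, and Table 2 lists it as recommendation adherence.
- **Intervention description {11a}:** controls receive nutrition lectures and printed material. In the account of the recommendation system, one month of tracking under natural conditions comes before any recommendation.
- **Sample size {14}:** "The power calculation is based on the primary outcome measure- dietary diversity score".
- **Statistical methods {20a}:** "We will use a two-sided significance level of 5% and report the results with two-sided 95% confidence intervals (CIs) for all statistical analyses". The repeated outcomes are analysed with a generalized linear mixed model whose main fixed effects are intervention and time.

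**The concern.** There are two problems, and the first is the more serious.

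**Adherence.** An outcome defined as agreement with recommendations needs recommendations to agree with. Sections {12} and {18a} require a baseline value and a control-arm value, and the definition supplies neither. A declared primary outcome therefore cannot be analysed as the protocol says it will be. Whoever runs the analysis would have to drop it, redefine it or invent control values, possibly after seeing data, in a trial where participants and researchers are unblinded.

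**Choice among the other two.** DDS and CDGI-E are both primary, at two times each, with no ranking and a 5% level throughout. If a favourable result on either were presented as the trial's primary finding, the chance of a false claim would exceed 5%. The outcome section also disagrees with the sample size section, which treats DDS alone as primary.

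**Working it through.** **Step 1. Can adherence be obtained where the protocol needs it?**

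| Needed by {12} and {18a} | Are recommendations present? | Source |
|---|---|---|
| Intervention arm, T0 | No; natural tracking comes first | {11a}, recommendation system |
| Intervention arm, T1 and T2 | Yes | {11a} |
| Control arm, T0, T1 and T2 | No; education only | {11a}, control group |

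Only one of the three rows yields a value. A change from T0 needs the first row and an arm contrast needs the third, so neither can be formed.

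**Step 2. Family-wise error for the two analysable outcomes.** Each test is at two-sided 5% ({20a}). The number of tests is not fixed by the protocol, so two cases are shown. Adherence is not counted, since a contrast that cannot be run adds no type I error.

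Independent tests:
- One test per outcome (2 tests): 1 − 0.95² = 0.0975
- T1 and T2 tested separately (4 tests): 1 − 0.95⁴ = 0.1855

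Correlated tests, from 400,000 multivariate normal draws. The correlation between time points is 0.7, taken from {14}. The correlation between DDS and CDGI-E is not in the protocol, so a range is assumed:

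| Assumed correlation, DDS with CDGI-E | 2 tests | 4 tests |
|---|---|---|
| 0 | 9.7% | 15.9% |
| 0.3 | 9.5% | 15.6% |
| 0.5 | 9.1% | 14.8% |
| 0.7 | 8.3% | 13.6% |

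The ranges are therefore about 8-10% for two tests and about 14-18.5% for four, the upper ends being full independence. In {14} the value 0.7 is the correlation among measures. With equal correlation, two changes that share a baseline correlate at 0.5, which would raise the four-test figures slightly.

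**Step 3. What a single DDS primary would need.** Inputs from {14}: δ = 2.3, σ = 6.12, ρ = 0.7, k = 3, two-sided α = 0.05, power 0.80.

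The plan's own figure first. The printed formula gives 2 × (1.960 + 0.842)² × 6.12² / (3 × 2.3²) = 37.05, so 38 per arm. The stated minimum is 60, which this does not reproduce; that is a separate matter. The attrition step does reproduce: 60 / 0.8 = 75 per arm, 150 in total.

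One visit at 6 months, ignoring clustering:
- Unadjusted: 2 × (1.960 + 0.842)² × 6.12² / 2.3² = 111.14, so 112 per arm.
- Power of that comparison at 60 per arm: 2.3 / (6.12 × √(2/60)) = 2.06, and Φ(2.06 − 1.96) ≈ 0.54.
- Adjusted for baseline, factor 1 − 0.7² = 0.51: 111.14 × 0.51 = 56.68, so 57 per arm.

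Average of T1 and T2 adjusted for baseline, factor (1 + 0.7)/2 − 0.7² = 0.36: 111.14 × 0.36 = 40.01, about 40 per arm, again ignoring clustering.

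**The case against.** **On adherence.** Section {12} speaks loosely of adherence to dietary interventions, so control adherence might be taken to mean lecture attendance. The operational definition rules this out: it compares chosen with recommended dishes, from the canteen system log. A reader might also infer that adherence could never exist for controls. That goes too far, because the algorithm could be run unseen for controls and for the tracking month, and concordance computed. But the protocol describes no such step, and agreement with unseen advice is not compliance in the sense of {11c}. The supportable statement is that the protocol gives no way to obtain these values.

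**On multiplicity.** The objection has more force here. A reader might infer that success on any of six comparisons (three outcomes at two times) counts, with an error rate of 1 − 0.95⁶ = 26.5% if independent. The document does not support this. It states no success rule, neither any nor all, and if every outcome had to succeed there would be no inflation. The six-test count also includes two adherence contrasts that cannot be run. The model in {20a} names intervention and time, with no separate tests at T1 and T2, so one test per outcome is a fair reading. Ranking and multiplicity control may also be set out in an analysis plan that is not shown.

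Nor is it right that the reader has no indication of the deciding outcome, since {14} points to DDS. What stands is that {12} and the abstract list unranked primaries, {14} names one, and {20a} applies 5% throughout. That is an inconsistency in the protocol's own text.

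**Conclusion.** The adherence contradiction is established from the text alone, needs no assumption and must be fixed: a declared primary outcome has no baseline and no control-arm value under its own definition.

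The multiplicity point is real but secondary and conditional. If success on either DDS or CDGI-E were claimed, the family-wise error would be about 8-10% with one test per outcome, or about 14-18.5% with separate T1 and T2 tests. These ranges rest on an assumed correlation between the two outcomes of 0 to 0.7 and on the protocol's 0.7 between time points, with full independence as the upper limit.

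**What to change.** 1. Remove adherence from the primary outcome. Report it as a process measure in the intervention arm, with no baseline. Correct the abstract, {12} and {18a} to match.
2. Name DDS as the single primary outcome, in line with {14}, with one contrast declared in advance: either the baseline-adjusted difference at 6 months or the overall intervention effect across follow-up.
3. Make CDGI-E the next test in a fixed sequence at 5%, or a key secondary outcome. Treat the remaining time-point contrasts as supportive.

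**Cost.** The change needs new wording, a registry update and the amendment route in {25}, with no extra participants or visits for this point. In a fixed sequence, CDGI-E can be claimed only if DDS succeeds. If the 6-month contrast is chosen, baseline adjustment is a condition of the fix: about 57 per arm are needed with it, against 112 without, and the unadjusted comparison has only about 54% power at 60 per arm. These figures use the inputs in {14} and make no allowance for site-level randomization, which would raise them.
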